### Randomization

Baseline data from the participants will be collected and evaluated before
enrollment. Healthy people will be numbered in the order of enrollment, while
the GAD patients will be randomly assigned to the TA group and SA group at a 1:1
ratio. To ensure a random distribution, randomization will be carried out by the
Institute of Acupuncture, which will not participate in this study. The assigned
random numbers and grouping results will be kept in opaque envelopes, which will
be kept by the staff not enrolled in this study and later opened by a research
assistant who will assign participants according to the order of patient
enrollment.

### Blinding

In this study, the acupuncturists cannot be blinded due to the particularity of
the acupuncture treatment, but the participants and the statisticians will be
blinded. Treatment, testing, and follow-up will be performed independently
without interaction between the groups. At the end of 8 weeks, participants in
the acupuncture and sham acupuncture groups will be asked the following
questions to test for blinding: “Are you confident with this treatment?” “Do you
accept this type of acupuncture?” Participants will choose either “Yes” or “No”
to answer the questions. These data will be analyzed at the end of the study. If
the results are not significant, then it can be concluded that blinding was
reliable. To ensure the consistency of treatment, the treatment and testing will
be completed by the same physician. The collectors of the data, the staff, and
the statisticians will not have access to the assigned tasks.

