### Primary outcomes

The primary outcomes of this study will be the HAMA and the single-pulse TMS
measures. The HAMA scale comprises 14 items, and assessment before and after
treatment is conducted by specialized psychiatric physicians. The HAMA total
score ranges from 0 to 56, with anxiety levels categorized as follows: possible
anxiety (8≤ total score ≤14), definite anxiety (14< total score ≤21),
moderate anxiety (21< total score ≤29), and severe anxiety (>29).
Single-pulse TMS is a common method for assessing changes in motor cortex
excitability. In this study, the key TMS parameters will include the amplitude
of MEPs, CSP, and RMT. The Magstim Rapid2 transcranial magnetic stimulation
device from Magstim (UK) and the Nicolet Viking Quest physiological recorder
from Natus Neurology Incorporated (USA) will be employed for measurements.
Single-pulse TMS will be applied with a maximum output intensity of 2.2 T,
corresponding to the first dorsal interosseous muscle. Changes in data will be
assessed before and after treatment for all participants including the RMT of
the motor cortex, the MEP-A, and the CSP. Efforts will be made to ensure that
assessments before and after treatment for all patients are conducted as close
as possible to the same time period.

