### Data collection and management

This study will collect basic information about eligible participants before the
first treatment, including name, age, gender, occupation, and course of disease.
During treatment and follow-up, medication and acupuncture reactions will be
recorded according to the participants' response. These data will be collected
at weeks 0 and 8. Data collection will be performed by three staff members who
are not involved in acupuncture treatment, index evaluation, statistical
analysis, or grouping. Data collection and entry work will be carried out
independently by two staff members and will be supervised and inspected by a
third staff member. Finally, they will complete the above work together.
Principal researchers, acupuncturists, TMS operators, and laboratory staff will
not be involved in data collection.

All data will be kept in paper documents and stamped with identification codes,
the electronic data will be stored on the clinical trial management public
platform ResMan Research Manager, and photographs will be named using
identification codes to ensure authenticity and integrity. All data will be kept
for at least 5 years. A data monitoring committee composed of experts with good
clinical research experience from the acupuncture Department of Shenzhen Bao'an
District Hospital of Traditional Chinese Medicine will regularly monitor
research progress, data, participant management, distribution, and more. The
Committee will be independent of the funding sponsor to avoid conflict of
interest. The researchers responsible for data collection and entry will have
access to the interim results and report to the principal investigator if
necessary. The principal investigators will make a final decision to terminate
the trial if so is decided after discussion.

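### The Blinding section gives treatment and testing to the same physician, which conflicts with the article's own role separation and leaves the week-8 TMS primary outcomes open to detection bias

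*Protocol article*

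**What the plan says.** All of the following is in the protocol article.

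- **Blinding**, on the treating staff: "the acupuncturists cannot be blinded due to the particularity of the acupuncture treatment".
- **Blinding**, on who is blinded: "the participants and the statisticians will be blinded". HAMA raters and TMS operators are not named here.
- **Blinding**, on who tests: "the treatment and testing will be completed by the same physician". The reason offered is consistency of treatment.
- **Blinding**, two other sentences: "Treatment, testing, and follow-up will be performed independently without interaction between the groups", and "The collectors of the data, the staff, and the statisticians will not have access to the assigned tasks".
- **Primary outcomes**: the HAMA and the single-pulse TMS measures are primary. For the HAMA, assessment before and after "treatment is conducted by specialized psychiatric physicians".
- **Data collection and management**: the sentence that begins "Principal researchers, acupuncturists, TMS operators, and laboratory staff will" keeps those groups out of data collection and lists acupuncturists and TMS operators as different people. The same section lists acupuncture treatment and index evaluation as different functions.

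**The concern.** The efficacy question is the TA versus SA comparison. The blunt-needle sham is there so that patients in the two arms hold similar expectations. It does nothing about the expectations of the person who measures the outcome. If that person also gave the real or sham needling, knowledge of the arm can enter the measurement itself. Blinding the statistician cannot remove such a bias afterwards.

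This is not a detail left to a fuller document. It is a positive instruction about who tests, and it cannot be followed together with other instructions in the same article. The Limitations section mentions differences in the timing of TMS measurements but not who performs them.

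**Working it through.** The article gives no figure that bears on this point, so the check sets its statements side by side.

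1. **Does the treating physician know the arm?** Yes. The Blinding section says so, and the interventions differ visibly to the operator: a penetrating needle in the TA group section, a blunt needle in a tube in the SA group section.

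2. **Does that physician test?** On the plain reading of the same-physician sentence, yes. Steps 1 and 2 together make the tester unblinded.

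3. **Does this agree with the rest of the article?**
   - *Data collection and management* separates acupuncturists from TMS operators, and treatment from index evaluation. One physician doing both does not fit. The explicit bar in that section concerns data collection only. It does not forbid an acupuncturist from performing TMS, so the conflict lies in the separate roles and functions, not in a broken prohibition.
   - *Primary outcomes* gives the HAMA to psychiatric physicians, who are not described as acupuncturists. Either testing includes the HAMA and the sections conflict, or testing means TMS only. The Trial status section does use the word testing for TMS.
   - *Blinding* closes by denying staff access to the assignments. A treating physician who also tests cannot satisfy that.
   - The sentence on independent performance carries little weight. In full it goes on to speak of interaction between the groups, so it may describe keeping the two arms apart and not treatment apart from testing.

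4. **Which outcomes are exposed?** Four primary measures are named: HAMA, MEP amplitude, CSP and RMT. The last three (4 − 1 = 3) are TMS measures and are exposed on either meaning of testing. The HAMA has its own named assessors, but nothing explicitly states that they are blinded. The serum markers are secondary, laboratory-measured and less affected.

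5. **Which time point?** The Randomization section places baseline evaluation before enrolment and assignment. Allocation is not known at week 0, so the exposure is at week 8.

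6. **Size.** The article gives no SD for any primary measure and nothing on how far an unblinded tester might shift one. No bias or false-positive rate can be calculated from it.

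**The case against.** The strongest reply is that the sentence is only badly worded. Its stated purpose is consistency, and it could mean that one physician treats throughout and one physician tests throughout. The separate roles in Data collection and management fit that reading, and the closing sentence of the Blinding section may be meant to cover testers under the word staff. This stands in part: the article does not prove that acupuncturists perform the tests. But it is not what the sentence says, and a site following it literally would have an unblinded tester. The word staff is too vague to override it.

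A reader might also infer more than the documents support.

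- *That all four primary outcomes are rated by the acupuncturist.* They are not shown to be. The HAMA is given to psychiatric physicians, and the gap there is only that their blinding is not stated.
- *That the sham control loses its value.* It does not. It still controls participant expectation, whoever does the testing.
- *That the inflation of false positives can be quantified.* Any figure would rest on an assumed SD and an assumed shift. For the HAMA it would also describe the outcome for which other assessors are named. The article shows no direction of shift for the TMS measures.

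**Conclusion.** The point holds in a limited form. The Blinding section contains a rule that, followed as written, puts a tester who knows the allocation on primary outcomes, and the rule conflicts with the roles set out elsewhere in the article. Exposure to detection bias is clearest for MEP amplitude, CSP and RMT at week 8 in the TA versus SA comparison. For the HAMA the gap is narrower: the assessors are different physicians, but they are not stated to be blinded. The conclusion rests on the plain reading of the same-physician sentence. If treatment and testing are in fact done by different people, the fault is one of wording, but it still needs correcting. The size of any bias is unknown.

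**What to change.** Delete the same-physician sentence and reconcile Blinding, Primary outcomes, and Data collection and management. Suggested text:

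*The HAMA is rated by the psychiatric physicians and TMS is performed by the TMS operators. None of them treats trial patients or has access to allocation. A given patient is measured by the same assessor at weeks 0 and 8.*

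The last sentence secures consistency of measurement without having the treating physician test. Add these assessors to the list of blinded parties.

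The Trial status section reports that recruitment is complete and that the GAD patients are still being treated and tested. The rule should therefore apply to every week-8 assessment still to come. For patients already assessed, record who tested each one.

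- If only some were tested by their treating physician, run a sensitivity analysis without them.
- If all or most were, that analysis would leave few or no GAD patients. Report unblinded TMS assessment as a limitation instead.

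The cost is an amendment to the wording, scheduling of the remaining assessments and a small amount of extra analysis. The roles needed are already named, although the article does not say whether enough people fill them.

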### Intervention

The protocol was designed based on previous clinical studies and basic theories
of TCM (12). All procedures complied with
the Acupuncture Clinical Trial Interventions Reporting Standards (STRICTA)
(13). According to the WHO Standard
and Acupoint Guidelines (14), acupoints
applied in the two groups will be the same, which are listed in Table 1 and Figure 3. All the acupuncturists in the study must have over 3 years
of relevant work experience. Before implementation, all the researchers will be
uniformly trained for this study. The HC group will not receive any treatment,
while two groups of GAD patients will receive 8 weeks of acupuncture treatment
for a total of 24 sessions. Patients will be asked to not use drugs or other
treatments that affect the study or have any other acupuncture treatment so as
not to interfere with the study evaluation of the effectiveness in the
study.

**Figure 3 f03:**
[figure not shown]
The six acupoints used in the study: BAIHUI (DU20), YINTANG (EX-HN3),
HEGU (LI4) (both sides), and TAICHONG (LV3) (both sides). Two are
applied on both sides.

**Table 1 t01:** Acupoints used in both the treatment with acupuncture (TA) group and
the sham acupuncture (SA) group.

Name	Location
YINTANG (EX-HN3)	At the forehead, mid-point between the two eyebrows.
BAIHUI (DU20)	On the median line of the head, 5 in. superior to the anterior hairline, at about the middle of the connecting line between both auricular tips.
HEGU (LI4)	On the back of the hand, between the first and second metacarpal bones, at the midpoint of the radial side of the second metacarpal bone.
TAICHONG (LV3)	On the dorsum of the foot, between the first and second metatarsal bones, in the depression in front of the metatarsal joint, or touching the artery where the pulse can be felt.

### TA group

Before undergoing acupuncture treatment, the patient will be asked to lie in the
flat supine position in a quiet environment. The acupuncturist will sterilize
the skin near the selected acupoints with 0.5% tincture of iodine or 75%
alcohol, then they will choose a one-time use stainless steel needle (25×25 mm,
Huatuo Suzhou, China) and insert it into the skin quickly. Needles will be
inserted in the YINTANG (EX-HN3), BAIHUI (DU20), HEGU (LI4), and TAICHONG (LV3)
points and twirled gently to “Deqi”, which is a therapeutic response to
acupuncture that refers to the sense of qi: the patient feels a heavy and
astringent feeling under the needle, with numbness, swelling, or heavy feeling.
After that, the needle will be retained for 30 min. The specific depth of
acupuncture depends on individual factors. When the needle is removed, the
acupuncturist will press the needle hole with a cotton swab for about 1 min to
prevent bleeding. Acupuncture treatment will be performed once a day, 3 times a
week for 8 weeks.

### SA group

The environment of the treatment, acupuncture location, and treatment frequency
of the SA group will be consistent with those of the TA group. The acupuncturist
will choose a blunt needle (20×25 mm, Huatuo Suzhou) for the SA group and attach
a translucent tube to the same acupoints as in the TA group. Then, the
acupuncturist will insert a blunt needle into the tube and hold the needle
upright. The patient will feel a mild stabbing sensation, but the needle will
not penetrate their skin.

### Basic western medicine

Paroxetine hydrochloride tablets (Leyou, 20 mg/day, 30 tablets per box) will be
prescribed to patients of the two treatment groups at the beginning of
acupuncture treatment and they will be required to take the medication under the
guidance of our psychologist.

### HA group

Healthy controls will not undergo any intervention.

### Outcome

TMS and biochemical measures will be used as measures of outcome. The main
observations include the amplitude of motor-evoked potentials (MEPs), cortical
resting period (CSP), resting motor threshold (RMT), and Hamilton Anxiety Scale
scores (HAMA), while serotonin (5-HT), glutamate (Glu), glutamine (Gln) in
peripheral serum, and γ-aminobutyric acid (GABA) and brain-derived nerve growth
factor (BDNF) will be used as secondary outcomes. Biospecimens will be kept at
-80°C after collection. All biological specimens will be analyzed in this assay
and used in future ancillary studies.

### Primary outcomes

The primary outcomes of this study will be the HAMA and the single-pulse TMS
measures. The HAMA scale comprises 14 items, and assessment before and after
treatment is conducted by specialized psychiatric physicians. The HAMA total
score ranges from 0 to 56, with anxiety levels categorized as follows: possible
anxiety (8≤ total score ≤14), definite anxiety (14< total score ≤21),
moderate anxiety (21< total score ≤29), and severe anxiety (>29).
Single-pulse TMS is a common method for assessing changes in motor cortex
excitability. In this study, the key TMS parameters will include the amplitude
of MEPs, CSP, and RMT. The Magstim Rapid2 transcranial magnetic stimulation
device from Magstim (UK) and the Nicolet Viking Quest physiological recorder
from Natus Neurology Incorporated (USA) will be employed for measurements.
Single-pulse TMS will be applied with a maximum output intensity of 2.2 T,
corresponding to the first dorsal interosseous muscle. Changes in data will be
assessed before and after treatment for all participants including the RMT of
the motor cortex, the MEP-A, and the CSP. Efforts will be made to ensure that
assessments before and after treatment for all patients are conducted as close
as possible to the same time period.

### Secondary outcomes

GABA and Glu, as the main inhibitory and excitatory neurotransmitters in the
brain, play a crucial role in the regulation and control of bilateral cerebral
cortex excitability, and the imbalance between them is considered to be the
basis of mental health diseases (15). Gln
is converted from Glu, 5-HT is the main substance to control emotions, and BDNF
has a high impact on brain plasticity. The quantitative detection of the above
five peripheral blood indicators before and after treatment will be used to
evaluate the efficacy of the treatment. All blood samples will be collected from
participants in a calm state on an empty stomach before 9 a.m.

### Sample size

The sample size for this study was estimated using the statistical data analysis
software PASS15 (NCSS Statistical software, https://www.ncss.com/support/). The parameters Z1-α and Z1-β
were consulted from tables, where πT represents the efficacy rate in the
observation group, πC represents the efficacy rate in the control group, and K
is the ratio of the number of cases in the treatment group to the control group,
set at 1. Due to the current lack of mechanistic studies on neuroplasticity in
patients with GAD and the absence of high-quality clinical research, we
established, based on literature review (16,17) and preliminary
trials, a control group efficacy rate of 70% and a treatment group efficacy rate
of 96%. A maximum acceptable difference of 15% in efficacy rates between the
observation and control groups was considered.

Through computations using the PASS15 software with parameters α=0.05 and β=0.2,
it was determined that a minimum of 29 cases per group was required. Since the
control group of healthy individuals does not require treatment, dropout issues
were temporarily disregarded. A total of 58 GAD subjects were required. Assuming
a ratio of 1:3 between the healthy and GAD patient groups, approximately 20
individuals in the healthy group were deemed necessary. Considering a potential
dropout rate of 10% in both groups receiving acupuncture treatment for GAD, each
group should include 33 participants, resulting in a total of 66
participants.

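### The 80% power and 29 per group rest on a binary efficacy rate that the article does not list as an outcome, and at the stated rates the 15% figure does not enter the calculation

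*Protocol article*

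**What the plan says.** The Sample size section takes from literature and preliminary "trials, a control group efficacy rate of 70% and a treatment group efficacy rate" of 96%, with equal allocation. It adds: "A maximum acceptable difference of 15% in efficacy rates between the" two groups was considered, without saying what role that figure plays. The error rates are given as "Through computations using the PASS15 software with parameters α=0.05 and β=0.2", and the result as "it was determined that a minimum of 29 cases per group was required". Allowing for 10% dropout gives 33 per group and 66 patients. The 20 healthy controls come from an assumed 1:3 ratio of healthy people to patients.

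The outcomes are set elsewhere. Under Primary outcomes: "The primary outcomes of this study will be the HAMA and the single-pulse TMS" measures, which are MEP amplitude, CSP and RMT. The Secondary outcomes section lists five blood markers. The Statistical analysis section plans analysis of variance or a rank sum test for continuous variables, and chi-squared or Fisher tests for categorical ones. It names no test against a margin.

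**The concern.** A power statement belongs to one outcome, one hypothesis and one test. Here it belongs to a difference between two proportions, while every listed primary outcome is a continuous measurement. The term efficacy rate occurs only in the Sample size section. The HAMA bands under Primary outcomes grade severity and do not define response. No mean difference or SD is given for any primary outcome, so the reader cannot convert the 80% into a statement about HAMA or TMS.

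The 15% figure adds a second difficulty. The language of an acceptable difference suggests a margin, yet the stated aim is to show that acupuncture works better than sham. A reader cannot tell from the text whether the calculation was for superiority, superiority by a margin, or non-inferiority.

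The interpretation of the results is at stake. A null HAMA or TMS finding could be read as coming from a trial with 80% power for that outcome, which the document does not support. The comparison of patients with healthy people is also a stated aim, and its size rests on a ratio alone.

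**Working it through.** **Inputs from the Sample size section:** control rate 0.70, treatment rate 0.96, difference 0.26, α = 0.05, β = 0.2, ratio 1:1, 15-point figure, 10% dropout. Sidedness is not stated. The notation in "The parameters Z1-α and Z1-β" hints at one-sided.

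**1. Reproducing 29.** Unpooled formula, two-sided, no margin:

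n = (1.960 + 0.842)² × [0.70×0.30 + 0.96×0.04] / 0.26² = 7.849 × 0.2484 / 0.0676 = 28.84, rounded up to **29**. This matches.

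Other no-margin versions do not give 29:

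- pooled two-sided: 32
- pooled two-sided with continuity correction: 39
- arcsine two-sided: 28
- unpooled one-sided: 23
- pooled one-sided: 25

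The two-sided reading is therefore inferred from the match. The rest of the chain also reproduces: 29/0.9 = 32.2, so 33 per group; 2 × 29 = 58; 58/3 = 19.3, so about 20 healthy controls.

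**2. Putting the 15 points in.** The numerator stays the same and the denominator changes.

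| Role of the 15 points | Denominator | One-sided 0.025 | One-sided 0.05 |
|---|---|---|---|
| Superiority by more than 15 points | (0.26 − 0.15)² = 0.0121 | 161.1, so 162 | 126.9, so 127 |
| Non-inferiority margin | (0.26 + 0.15)² = 0.1681 | 11.6, so 12 | 9.1, so 10 |

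If 15 points were instead the difference to detect (two-sided, pooled), the need would be 121 per group for 70% against 85%, or 70 per group for 81% against 96%. None of these gives 29.

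**3. What the fixed size can detect on a continuous outcome.** Two-sample t-test, two-sided 0.05, 80% power. The normal approximation is d = 2.802 × √(1/n₁ + 1/n₂); the last column uses the t distribution.

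| Comparison | Normal approximation | t-based |
|---|---|---|
| 29 vs 29 | 2.802 × √(2/29) = 0.736 | 0.749 SD |
| 33 vs 33 | 2.802 × √(2/33) = 0.690 | 0.700 SD |
| 58 GAD vs 20 healthy | 2.802 × √(1/58 + 1/20) = 0.727 | 0.736 SD |
| 66 GAD vs 20 healthy | 2.802 × √(1/66 + 1/20) = 0.715 | 0.723 SD |

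**4. Sensitivity to an assumed effect.** The documents give no standardised difference, so the values below are assumptions, shown as a range.

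| Assumed difference | Power, 29 per group | Power, 33 per group |
|---|---|---|
| 0.4 SD | 32% | 36% |
| 0.5 SD | 46% | 52% |
| 0.6 SD | 61% | 67% |
| 0.7 SD | 75% | 80% |
| 0.8 SD | 85% | 89% |

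**The case against.** The arithmetic is sound: 29, 33, 58, 66 and about 20 all reproduce. This is also a condensed article. A response definition derived from HAMA may sit in the full protocol, and the Ethics and dissemination section warns that its indicators do not match the registered programme completely. This stands in part. The right statement is that the rate is not listed or defined in this document, not that the trial has no such outcome. It does not remove the mismatch, because the article gives both the primary outcomes and the power claim, and the two do not meet.

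A reader might infer that the trial has less than 80% power for HAMA or TMS. The documents do not support that. They give no SD and no expected difference, and with 33 per group the power is 80% or more if the true difference is at least 0.70 SD.

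A reader might also infer that Fisher's test would leave the comparison of rates underpowered. That fails at the planned size: expected failures per cell are 33 × 0.17 = 5.6, above the usual threshold of 5, and the uncorrected chi-squared test then has exact power of 0.87 on the assumed rates.

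That the 15% cannot have been used holds only at 70% and 96%. Non-inferiority with 96% in both arms and a 15-point margin would need 27 per group (one-sided 0.025). That is close to 29, but it discards the stated 70% and the superiority aim.

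For the healthy controls, the article states the 1:3 basis openly and claims no power, and its limitations paragraph calls the research exploratory. That comparison carries no false claim; a detectable difference would simply make it readable.

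**Conclusion.** The point holds in this form: the stated 80% power attaches to a binary rate that this document does not list or define as an outcome, so it is not established for any listed primary outcome. At the stated rates the 15% figure does not enter the 29. Including it as a margin would move the requirement to 127–162 or to 10–12 per group.

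The fault is a mismatch between endpoint and sample size plus an unexplained margin, not a computing error. The conclusion on the 15% rests on the stated 70% and 96% and on a two-sided test inferred from the exact match. The detectable differences assume a two-sample t-test at two-sided 0.05 for a single outcome. The 46–52% power at 0.5 SD rests on an assumed effect and is illustration only.

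**What to change.** Keep 33 per group. Recruitment is complete according to the Trial status section, so the size is settled and only its justification changes.

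- Replace the power statement with the detectable difference, labelled as calculated for a size already fixed. For example: *With the sample size fixed, a continuous primary outcome has 80% power at two-sided 0.05 for a between-group difference of 0.75 SD with 29 completers per group, or 0.70 SD with 33; for GAD patients against 20 healthy controls the corresponding figure is about 0.72 to 0.74 SD.* The label matters, because a difference worked back from n says nothing about whether that effect is plausible or clinically relevant.
- State that the hypothesis is superiority, and that the test is two-sided if that was intended.
- Delete the 15% figure, or explain what it is and where it is used.
- Either define the efficacy rate (for example from HAMA) as a secondary outcome with a planned test, or drop the 80% claim based on 70% against 96%.

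The cost is wording only, with no extra patients or measurements, and it can be done before analysis. The price is a less favourable statement: an unconditional 80% becomes 80% for a difference of 0.70 to 0.75 SD.
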